## 2. Materials and Methods

### 2.1. Design and Description of the Programme and Its Contents

Following other studies targeting caregivers of people with dementia, a telephone- and Internet-based intervention is proposed [36]. In line with previous studies [34,35], the CAREFIT programme will be developed using WordPress, a widely used content management system (CMS) running PHP and MySQL. According to W3Techs [37], more than 28% of the top ten million websites use this platform. Thanks to its open-source nature and large community of developers, WordPress offers solid online support and a great capacity for expansion through plugins.

The main menu will be divided into sections for physical, educational, psychoemotional health, and social support activities.

The physical activities section will include sessions with a variety of exercises, ranging from stretching to exercises aimed at improving strength, balance, or endurance. All sessions will feature videos guided by an avatar, who will time each exercise and session. This avatar will narrate the objective and key points for the execution of each exercise before it starts, as well as the beginning and end of the exercise. For each exercise, there will be three levels (basic, intermediate, and advanced) that can be selected by the participant prior to execution, thus adapting to their level.

The educational section will provide training on the benefits of healthy living habits, resources on self-care and family care, as well as on how to incorporate these into ADLs or daily life, based on multimedia presentations and interactive or animated infographics or videos.

The psychoemotional support section will offer resources to prevent caregiver burden, stress, anxiety, and depression.

The social support section will offer resources and tips for caregivers, such as information on support networks, dependency care services, and strategies for managing stress, overload, and self-care.

The planning of the interventions is presented in Table 1.

In addition, to measure adherence to the intervention, an electronic tracking system will be used to monitor participants’ attendance rates at sessions, the completion of tasks or activities, and the percentage of participants who complete the programme compared to those who started it. Throughout the intervention, the research team will be in frequent contact with the participants through phone calls and messages in order to provide support and motivation, thus encouraging their involvement in the process. In addition, participants will receive a monthly report summarising their progress and achievements.

### 2.2. Randomised Controlled Trial

#### 2.2.1. Desing

A Randomised Controlled Trial (RCT) will be conducted, designed following the Consolidated Standards of Reporting Trials (CONSORT) [38] for the conduct of this type of design. It will comprise an 8-week intervention phase, including an assessment at baseline, an assessment upon completion, and a follow-up assessment one month after the end of the programme. Random sampling will be used. Participating caregivers will be randomly assigned to either the intervention (experimental) or the “usual care” (control) group.

#### 2.2.2. Ethics

Ethical approval for this study was obtained from the Bioethics and Biosafety Committee of the University of Extremadura, with approval number (145/2024). This ensures that the research adheres to the highest ethical standards, prioritising the welfare and rights of all participants involved. In addition to institutional approval, the study protocol has been registered with OFS (osf.io/93trc). This registration serves to increase transparency and accountability in the research process by allowing public access to the details and methodology of the study. By obtaining both ethics approval and trial registration, the study aims to uphold the principles of ethical conduct in research, ensuring that participant safety and informed consent are prioritised throughout the duration of the trial. This commitment to ethical standards is essential to foster trust and integrity in the research community.

#### 2.2.3. Sample Calculation

The calculation of the number of participants needed for this study was based on the expected change in quality of life as measured by the EQ-5D-5L questionnaire. Since, to our knowledge, there are no specific data on the minimum clinically relevant change in informal caregivers using this instrument, a minimum difference of 0.07 units was taken as a reference value [39]. Considering a significance level (alpha) of 0.05 and a statistical power greater than 0.8 in a two-sided test, it was determined that 25 participants in the control group and 25 in the experimental group are needed to identify a difference equal to or greater than 0.07 units as significant. A common standard deviation of 0.12 [40] and a correlation coefficient of 0.8 between the initial and final measurements were assumed. In addition, an estimated dropout rate of 25% was calculated. The calculation was performed using version 7.12 of the GRANMO to determine the sample size. (https://www.datarus.eu/aplicaciones/granmo/ (accessed on 10 January 2025)).

#### 2.2.4. Participants

Informal carers of people with dementia will be recruited from specific associations and social and healthcare centres by the means of non-probabilistic convenience sampling. For this purpose, project information sessions will be held at the different associations and socio-health centres in the region, and leaflets will be distributed for recruitment. The research team will identify potential participants and assess them for eligibility according to the inclusion criteria specified below.

Participants have to be a primary informal caregiver of a person with a diagnosis of dementia, dedicating more than 20 h per week to this task for a minimum of three months, and be willing to continue providing care for the next year. They cannot have taken part in or received any type of psychoeducational or cognitive–behavioural therapy-based intervention in the three months prior to the start of the study. They must complete and sign both the informed consent and the acceptance document to participate in the study. They must have a mobile device or, failing that, a tablet or computer.

#### 2.2.5. Intervention

After completing the initial assessments, all participants will be randomly allocated between the experimental intervention group and the control group. To assign participants, a random sequence will be generated in a 1:1 ratio, which will assign participants to either the experimental or control group. This will be performed using Research Randomizer software (version 4.0, Geoffrey C. Urbaniak y Scott Plous, Middletown, CT, EE. UU.; http://www.randomizer.org (accessed on 16 June 2024)) [41]. This allocation will be performed by a member of the research team who has no clinical involvement in the study. The allocation information will be stored confidentially in a password-protected file. Although participants will know which group they have been assigned to, outcome assessors and data analysts will have no knowledge of their assignment. The experimental group will develop the intervention programme, which will last 8 weeks and will combine educational activities, physical activities, and psychoemotional and social support. The programme will be designed to be flexible and adaptable to the individual needs of the caregivers. Before starting the intervention, the entire experimental group will receive a training session and training material on how to access and use the platform. In addition, once a week, a member of the research team will have a telephone or video call with each participant to solve doubts or technical problems and to follow up in order to adjust the intervention to the individual needs or personal situations of each caregiver. The CAREFIT platform will contain 2 educational sessions and 2 physical sessions per week combined with psychoemotional and social support activities to be completed by the participants. The control group will carry out their usual daily activities. The flow chart for the RCT is shown in Figure 1.

#### 2.2.6. Measurements and Instrument

The measures to be carried out will consist of a questionnaire booklet that will include the assessment of socio-demographic data (age, sex, level of education, income, occupation, marital status, life habits, and pathologies), HRQoL, caregiver burden, occupational balance, satisfaction with daily occupations, depressive symptoms, anxiety, stress, and perceived social support.

The following instruments will be used for this purpose:(1)Quality of life
EQ-5D-5L. This questionnaire measures the health status of participants and is divided into the following three assessments: (1) the assessment of several dimensions of health (mobility, self-care, activities of daily living, pain/discomfort, and anxiety/depression) using a descriptive Likert-type system from 1 to 5 points (no problems to problems/external impossibility); (2) the assessment of health status using a visual analogue scale; and (3) the assessment of social value using an index generated from the health states obtained in the first level [42]. It is a valid and reliable questionnaire both in the Spanish population [43] and in other populations [44] and in caregivers of people with other pathologies, with a validity of 0.987 [45].
(2)Stress
Perceived Stress Scale (PSS) [46]. This scale will measure perceived stress and consists of 14 questions that measure the degree to which situations in a person’s life are rated as stressful. The questions are formulated in terms of feelings and thoughts over the last month, and participants are asked to rate the frequency with which they have experienced them on a 5-point Likert scale. The score will be used to assess the participants’ level of stress. This scale showed a good reliability in the Spanish population, with a Cronbach’s alpha 0.82 [47].
(3)Anxiety and depressionGeneral Health Questionnaire (GHQ-12) [48]. This scale will be used for the assessment of depression and anxiety. It is composed of 12 items (Yes/No). The cut-off point for the anxiety subscale is 4 or more points and 2 or more points for the depression subscale. Higher point values indicate a more severe problem, with 6 being the highest possible value for each subscale. The internal consistency analysis in Spanish population yielded an alpha coefficient of 0.78 [49].Geriatric Depression Scale (GDS). This questionnaire will measure depression and consists of 15 questions about how the participant has been feeling in the last 14 days, with the answers limited to ‘yes’ or ‘no’. The internal consistency analysis yielded an alpha coefficient of 0.87 [50].
(4)Caregiver burdenZarit Burden Inventory (ZBI) (Spanish version). This 22-item questionnaire quantifies caregiver strain. This scale consists of 22 items in a Likert scale format, using a scale from one (never) to five (almost always). The recommended cut-off points are as follows: <46 indicating no caregiver burden; 46 to 56 items indicating mild caregiver burden, and >56 items indicating severe caregiver burden. Its internal consistency is high, with a Cronbach’s alpha coefficient of 0.91 [51].
(5)Occupational balanceOccupational Balance Questionnaire (OBQ-E). This questionnaire assesses participants’ satisfaction with their occupations by the means of 13 items, answered on a Likert scale from zero ‘strongly disagree’ to five ‘strongly agree’. The internal consistency obtained a value of Cronbach’s alpha of 0.948 [52].
(6)Perceived social supportFunctional Social Support Questionnaire DukeUNC-11 [53]. This instrument consists of 11 items that are answered on a Likert scale from 1 to 5, where 1 represents ‘much less than I want’ and 5 ‘as much as I want’, where the questionnaire score ranges from 11 to 55 points. A score of 32 or above indicates standard social support, while a score below 32 suggests low perceived social support. In the Spanish population, the internal consistency of the questionnaire was found to be high, with a consistency coefficient of 0.90 [53].

Assessments will be conducted before the start of the intervention (baseline), at the end of the intervention (8 weeks), and one month after the end of the intervention (12 weeks) (Table 2).

#### 2.2.7. Statistical Analysis

The data will be analysed with the computer programme IBM Social Sciences (SPSS, version 25.0, Armonk, NY, USA). The normality and homogeneity of the data will be examined by Levene and Kolmogorov–Smirnov tests, respectively. The baseline and socio-demographic characteristics of the study participants will be presented for categorical variables as frequencies and percentages and for continuous variables as means and standard deviations.

The effects of the intervention on the study variables, HRQoL, physical condition, and psychoemotional state (stress, anxiety, depression, caregiver strain, and perceived social support), will be assessed by repeated-measures analysis of variance (ANOVA). The results of the study will incorporate the effect size, together with its corresponding 95% confidence interval, as well as the statistical significance for each measure analysed, considering both the evolution over time and the interaction effects between group and time. If the data do not follow a normal distribution, the Friedman test will be applied. Statistical significance will be established at the conventional level of *p* < 0.05.

In the case of missing data, the Intention-To-Treat (ITT) strategy will be used to maintain the original randomisation and reduce the risk of bias by analysing all participants according to the group to which they were assigned, regardless of their level of adherence.

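### The trial is sized on one between-arm difference in baseline-to-week-8 EQ-5D-5L change, but its effect is to be read from a pooled time effect and a three-visit group-by-time interaction

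*Protocol article*

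**What the plan says.** Section 2.2.3 of the Protocol article states that the sample size is "based on the expected change in quality of life as measured by the EQ-5D-5L questionnaire". Its inputs are:

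- the target difference: "a minimum difference of 0.07 units was taken as a reference value"
- the spread: "A common standard deviation of 0.12"
- the link between visits: "a correlation coefficient of 0.8 between the initial and final measurements were assumed"
- the error rates: "Considering a significance level (alpha) of 0.05 and a statistical power greater than 0.8 in a two-sided test"

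With a 25% dropout rate, the result is that "25 participants in the control group and 25 in the experimental group are needed".

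Section 2.2.6 and Table 2 schedule every outcome scale at baseline, "at the end of the intervention (8 weeks), and one month after the end of the intervention (12 weeks"). Final therefore means week 8, and there are three visits.

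Section 2.2.7 assesses the effects of the intervention by repeated-measures ANOVA at p < 0.05. It promises an effect size with a 95% confidence interval and a significance test for each measure, "considering both the evolution over time and the interaction effects between group and time". It does not say which visit or contrast the effect size refers to, and it does not mention baseline as a covariate. The hypothesis at the end of the Introduction is a comparison with caregivers who do not take part.

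**The concern.** The sample size and the analysis answer different questions. The first concerns one number: how much more the EQ-5D-5L index changes from baseline to week 8 in one arm than in the other. The second yields two tests, and neither is that number.

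The time main effect averages the two arms. It shows whether caregivers as a whole changed, which can happen through natural course, regression to the mean or repeated questioning. It carries no information on whether the programme helped. Section 2.2.7 nevertheless places it beside the interaction as a result by which the intervention is assessed.

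The interaction does compare the arms. With two groups and three visits it has 2 numerator degrees of freedom, and it asks whether the two profiles differ in shape anywhere. A significant result does not say at which visit or in which direction the arms differ. Its power depends on the week-12 effect and on correlations with week 12, and the sample-size section gives neither.

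**Working it through.** **Inputs from section 2.2.3.** Difference d = 0.07, SD = 0.12, baseline–final correlation ρ = 0.8, two-sided α = 0.05, power 0.80, dropout 25%. With 25 randomised per arm, 25 × 0.75 = 18.75, so about 19 are evaluable.

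**1. Reproducing the plan's figure.** The SD of the change score is 0.12 × √(2 × (1 − 0.8)) = 0.0759.

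n per arm = 2 × (0.0759 × (1.960 + 0.842) / 0.07)² = 18.45, and 18.45 / 0.75 = 24.6, so 25. The stated sample size is a two-arm comparison of change scores. Two alternatives do not give 25:

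- Final scores without baseline (SD 0.12): 47 evaluable per arm, 63 with dropout.
- Baseline-adjusted comparison (SD 0.12 × √(1 − 0.8²) = 0.072): 16.6, so 17 evaluable per arm; 17 / 0.75 = 22.7, so 23.

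**2. Week-8 comparisons with 19 per arm.**

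- Change score: noncentrality 0.07 / (0.0759 × √(2/19)) = 2.84. Power is 0.79 by the t distribution (36 df) and 0.81 by the normal approximation.
- Baseline as covariate (ANCOVA): noncentrality 0.07 / (0.072 × √(2/19)) = 3.00. Power is 0.83 by the t distribution (35 df) and 0.85 by the normal approximation.

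In units of SD², the residual variance is 2 × (1 − 0.8) = 0.40 for the change score and 1 − 0.64 = 0.36 for ANCOVA, a 10% reduction. Neither result involves week 12.

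**3. Group-by-time interaction with 19 per arm.** The effect is 0.07 at week 8. The week-12 effect and the correlations with week 12 are assumptions. With all correlations 0.8, the noncentrality is

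λ = (n/2) × Σ(effect − mean effect)² / (SD² × (1 − ρ)), with 2 and 72 df and SD² × (1 − ρ) = 0.0144 × 0.2 = 0.00288.

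- Fully kept (0, 0.07, 0.07) or wholly lost (0, 0.07, 0): sum of squares 0.00327, λ = 9.5 × 0.00327 / 0.00288 = 10.8, power 0.83.
- Half kept (0, 0.07, 0.035): sum of squares 0.00245, λ = 9.5 × 0.00245 / 0.00288 = 8.08, power 0.70.

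Unequal correlations were simulated (5,000 runs per case, Greenhouse–Geisser correction):

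| Correlations (baseline–8, 8–12, baseline–12) | Effect fully kept at week 12 | Half kept | Wholly lost |
|---|---|---|---|
| 0.8, 0.8, 0.8 | 0.83 | 0.70 | 0.83 |
| 0.8, 0.9, 0.72 | 0.74 | 0.66 | 0.87 |
| 0.8, 0.8, 0.64 | 0.67 | 0.56 | 0.76 |

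**4. Time effect when the programme does nothing.** Both arms shift equally by c at weeks 8 and 12, all correlations are 0.8, and 38 people are evaluable: λ = 38 × (2/3)c² / 0.00288.

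- c = 0.03: λ = 7.9, significant with probability 0.69.
- c = 0.05: λ = 22.0, significant with probability 0.99.

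**The case against.** The group-by-time interaction is a legitimate randomised comparison, and section 2.2.7 includes it. Repeated-measures ANOVA is not invalid here, and the baseline-to-week-8 contrast can be obtained from the same model. The promised effect size with its interval could be that contrast. The article condenses a fuller plan, and follow-up contrasts or covariates may be set out there. The sentence on time and interaction lists what will be reported and does not claim that a time effect alone proves efficacy. All of this stands, and it rules out several stronger readings:

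- A reader might infer that the planned test wastes power. The documents do not support that as a general statement. With equal correlations and an effect fully kept or lost, the interaction matches ANCOVA (0.83) and exceeds the change-score test (0.79); in one scenario it reaches 0.87.
- A reader might infer that the trial was sized on a baseline-adjusted difference. It was sized on a change score; the adjusted calculation gives 23 per arm, not 25.
- A reader might infer that the stated power above 0.8 fails and that ANCOVA restores it. The change-score figure is 0.79 by the t distribution and 0.81 by the normal approximation, so the claim reproduces to within the choice of approximation.

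The objection does not answer two points. The article puts a pooled time effect and a between-group interaction side by side as ways of assessing the intervention, without separating their meaning. It also sizes one contrast and then does not name that contrast in the analysis.

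**Conclusion.** The concern holds as a mismatch between sizing and analysis, not as an invalid test. The more serious part is the time effect: a shared improvement of 0.03 with no programme effect would make it significant about 69% of the time, so it must not count towards efficacy. The second part is that power under the interaction is not fixed by what section 2.2.3 assumes. It runs from 0.56 to 0.87 over the scenarios tried, whereas a baseline-adjusted week-8 comparison stays at about 0.83.

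These figures rest on the article's SD of 0.12, difference of 0.07 and baseline–final correlation of 0.8, with 19 evaluable per arm. The week-12 effects and correlations, and the shared changes of 0.03 and 0.05, are assumptions. The gain from adjusting for baseline rather than taking change scores is modest at a correlation of 0.8 (0.79 to 0.83, t-based) and is an efficiency gain, not the correction of an error.

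**What to change.** For EQ-5D-5L, the outcome on which the trial was sized, state in section 2.2.7 that the deciding contrast is the between-group difference at week 8 with the baseline score as covariate. This can be an ANCOVA or the week-8 contrast of a baseline-adjusted mixed model. Report it in index units with its 95% confidence interval, so that it can be set against 0.07. Report the week-12 difference as a secondary contrast, and say that the time main effect is descriptive and is not evidence of efficacy. The same baseline adjustment can be used for the other scales; how those outcomes rank against EQ-5D-5L is a separate matter.

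The cost is a change of wording. Baseline is already measured before randomisation, no new data are needed, and 25 per arm exceeds the 23 that the adjusted comparison requires with 25% dropout.

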To the best of our knowledge, there have been studies that intervened through psychoeducational [27,28] or cognitive–behavioural [29,30] programmes for caregivers of people with dementia or publications on didactic exercise interventions in people with dementia and their caregivers [31,32], as well as some educational, psychoemotional, and physical interventions whose medium of application was the internet [24]. In addition, there is evidence that programmes including educational modules, forums and real-time support sessions [33], and eHealth psychoeducational programmes aimed at increasing knowledge of neurocognitive disorders, their management at home, and the presence of national support services [34] have significantly reduced the level of behavioural symptoms in patients with dementia, increased empowerment, and eased the burden on caregivers, thus improving their caregiving skills. There are even interventions that have evaluated the effectiveness of an online psychoeducational programme combined with an immersive virtual reality (VR) experience in reducing caregivers’ perceived stress by acting on the cognitive and affective components of empathy [35]. However, there is no study that has used technological means to carry out an interdisciplinary programme with PA interventions together with health literacy for informal caregivers of people with dementia. Therefore, the aim of this project is to determine the effect of an 8-week intervention programme based on the CAREFIT (Caregivers’ Active Resilience & Exercise for Fitness and Well-being) programme on the HRQoL and psychoemotional health (stress, anxiety, depression, and perceived social support and caregiver burden) of caregivers of people with dementia.

In this sense, the hypothesis of the study protocol is that the implementation of an 8-week intervention programme based on the CAREFIT model will improve health-related quality of life (HRQoL) and psychoemotional health indicators (decreased stress, anxiety, depression, and overload, as well as increased perceived social support) in caregivers of people with dementia, compared to those who do not participate in the programme.

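### The only fallback named for non-normal data is the Friedman test, which has no group term, so any outcome analysed that way gets no comparison of the randomised arms

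*Protocol article*

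**What the plan says.** The hypothesis, at the end of section 1 (Introduction), is that the programme improves quality of life and psychoemotional health "compared to those who do not participate in the programme". Section 2.2.5 sets up two parallel arms: "a random sequence will be generated in a 1:1 ratio, which will assign participants to either the experimental or control group". Section 2.2.6 places assessments at baseline, 8 weeks and 12 weeks. Section 2.2.3 sizes the trial at 25 per arm to detect a 0.07 difference on the EQ-5D-5L.

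Section 2.2.7 plans a repeated-measures ANOVA and promises an effect size, a 95% confidence interval and a significance result for each measure, "considering both the evolution over time and the interaction effects between group and time". It then gives the rule for non-normal data: "If the data do not follow a normal distribution, the Friedman test will be applied". No second test accompanies it. The check that leads to this rule reads: "The normality and homogeneity of the data will be examined by Levene and Kolmogorov–Smirnov tests, respectively".

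**The concern.** The hypothesis, the allocation and the sample size all concern a difference between arms. The Friedman test is a one-way test of change across related measurements. It can say whether scores differ between visits, but not whether they change differently in the two arms.

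The sentence does not say whether the test would be run on both arms together or within each arm, and neither version helps. Pooled, it can turn a time trend shared by both arms into a significant result. Run by arm, it invites the invalid inference that a significant result in one arm and a non-significant result in the other shows a treatment effect. In either case the randomisation is not used for that outcome.

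**Working it through.** **Inputs.** From section 2.2.3: difference 0.07, SD 0.12, baseline-to-final correlation 0.8, two-sided alpha 0.05, power above 0.8, dropout 25%, 25 per arm. From section 2.2.6: three visits.

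**1. What the sample size was built for.**
- SD of change = 0.12 × √(2 × (1 − 0.8)) = 0.0759.
- n per arm = 2 × (0.0759 × (1.960 + 0.842) / 0.07)² = 18.45, so 19 evaluable.
- Allowing for dropout, 18.45 / 0.75 = 24.6, so 25.

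The stated 25 reproduces as a comparison of change between two arms. (Inflating the rounded 19 gives 26, which is only a rounding difference.)

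**2. What the Friedman test uses.** With N people and k visits, and R_j the sum over people of the within-person ranks at visit j,

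Q = 12 / (N k (k + 1)) × Σ R_j² − 3N(k + 1).

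For k = 3 this is Q = Σ R_j² / N − 12N, referred to chi-squared on 2 degrees of freedom. No arm index appears. If the pooled participants were relabelled at random between the arms, Q and its p-value would not change. A statistic that ignores the arm labels cannot test group or group-by-time.

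**3. Size of the consequence.** Simulated trials (2,000 to 5,000 per scenario, over repeated runs) used SD 0.12, correlation 0.8 and 19 to 25 per arm. Three assumptions are not in the documents: normal data, the same correlation between every pair of visits, and shifts that are equal at both later visits. Normal data are used only to show what the test responds to.

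| Shift, experimental / control | True difference | Pooled Friedman rejects | Mann-Whitney on change rejects |
|---|---|---|---|
| 0 / 0 | 0 | about 5% | about 5% |
| +0.01 / +0.01 | 0 | 9–12% | about 5% |
| +0.02 / +0.02 | 0 | 25–34% | about 5% |
| +0.04 / +0.04 | 0 | about 80–90% | 4–5% |
| +0.07 / 0 | 0.07 | 56–72% | about 75–87% |
| +0.035 / −0.035 | 0.07 | 3–4% | about 75–87% |

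The lower end of each range is generally 19 per arm and the upper end 25. With the test run by arm, no treatment effect and a common shift of 0.04, the experimental arm alone is significant in about 22–26% of trials. A valid between-group test would be wrong in 5%, counting both directions.

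The pooled rejection rate follows the average movement of the two arms. It is high in row 4, where the arms do not differ, and lowest in row 6, where they differ by the full target.

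**4. Whether the branch is realistic.** Section 2.2.6 includes two GHQ-12 subscales with a maximum of 6 and a depression scale of 15 yes/no items. It also includes wider sums: 22 burden items, 14 stress items, 13 occupational balance items and a social support score from 11 to 55. For a continuous score at N = 50, a Kolmogorov–Smirnov test of the Lilliefors type rejects normality in 12%, 66% and 97% of simulated samples when 10%, 20% and 30% of people are at the ceiling. Those shares are assumptions, since the documents give none.

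**The case against.** The main analysis is sound. The ANOVA interaction is a valid randomised contrast, and the promise to report group-by-time effects for each measure comes before the Friedman sentence and is not limited to normal data. The sentence could be read as naming only the rank counterpart of the within-person part, with a between-group rank test placed in a fuller plan that is not shown. This stands to the extent that the loss is conditional and arises outcome by outcome. A reader might infer that the trial has no randomised comparison at all, and the text does not support that. It does not rescue the sentence, however: the article names a specific test for this case, and that test cannot deliver the promised interaction.

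Four further inferences go too far.
- *The fallback would miss a real effect.* The 3–4% figure needs the arms to move symmetrically in opposite directions. The protocol expects improvement against usual activities, and if only the experimental arm moves the pooled test rejects in 56–72%. Such a rejection still cannot be attributed to group, because a shared trend produces the same result.
- *A false signal is near certain.* The 80–90% figure needs both arms to gain 0.04, more than half the target difference. Nothing in the documents predicts this, and the rate falls to 9–12% at a shift of 0.01.
- *The fallback will almost surely be used.* That depends on ceiling shares or skewness that the documents do not give, and several outcomes are wide sums.
- *The normality check is unworkable.* As worded, Levene is assigned to normality and Kolmogorov–Smirnov to homogeneity, which is reversed. Both tests and both properties are named, so this is most probably a word-order slip.

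**Conclusion.** The fallback rule is wrong as written. For any outcome judged non-normal, the named test does not make the comparison that the hypothesis, the sample size and the promised interaction require. This follows from the structure of the test and depends on no simulation assumption.

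The size does depend on assumptions. With no treatment effect, pooled rejection runs from the nominal 5% to about 80–90% according to the common time trend. With a true 0.07 difference it runs from 3–4% to 56–72% according to which arm moves. How often the branch would be taken cannot be determined from the documents; the short bounded scores make it a realistic possibility and no more. The planned ANOVA and the sample size of 25 per arm are not called into question by this point.

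**What to change.** Replace the Friedman sentence in section 2.2.7 with a fallback that compares the arms. Either of these would do:
- a rank comparison of change from baseline between arms (Mann-Whitney), or a rank ANCOVA; or
- the planned group-by-time contrast, kept, with bootstrap or robust confidence intervals.

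If the Friedman test is retained, limit it to describing change within an arm and state that it is not evidence of a treatment effect. The repeated-measures ANOVA does not have to be replaced by another model to cure this defect.

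As an editorial correction, assign Kolmogorov–Smirnov to normality and Levene to homogeneity of variance.

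The cost is two sentences, with no extra participants, visits or data. With 19 evaluable per arm and under the assumptions above, Mann-Whitney on change has about 75% power at a 0.07 difference, against about 79% for the t-test on change.
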